## Abstract

**Background:**

Unhealthy infant feeding practices, such as a combination of formula feeding and early introduction of solids may lead to rapid or excessive weight gain in early infancy. Adolescent mothers’ feeding behaviors are most directly related to infant weight gain in the first year of life. Compared to adult mothers, adolescent mothers are less knowledgeable, less responsive, more controlling, and less skilled in infant feeding, which interferes with infants’ healthy growth. The Tools for Teen Moms trial aims to compare the effect of a social media intervention for low-income adolescent, first-time mothers of infants 2 months of age or younger, versus standard care on infant weight, maternal responsiveness, and feeding style and practices. The intervention is conducted during the infant’s first four months of life to promote healthy transition to solids during their first year. Tools for Teen Moms is an intervention delivered via a social media platform that actively engages and coaches low-income adolescent mothers in infant-centered feeding to reduce rapid/excessive infant weight gain in the first six months of life.

**Methods/Design:**

We describe our study protocol for a randomized control trial with an anticipated sample of 100 low-income African- American and Caucasian adolescent, first–time mothers of infants. Participants are recruited through Maternal-Infant Health Programs in four counties in Michigan, USA. Participants are randomly assigned to the intervention or the control group. The intervention provides infant feeding information to mothers via a web-based application, and includes daily behavioral challenges, text message reminders, discussion forums, and website information as a comprehensive social media strategy over 6 weeks. Participants continue to receive usual care during the intervention. Main maternal outcomes include: (a) maternal responsiveness, (b) feeding style, and (c) feeding practices. The primary infant outcome is infant weight. Data collection occurs at baseline, and when the baby is 3 and 6 months old.

**Discussion:**

Expected outcomes will address the effectiveness of the social media intervention in helping teen mothers develop healthy infant feeding practices that contribute to reducing the risk of early onset childhood obesity.

**Trial registration:**

Clinical Trials.Gov NCT02244424, June 24, 2014

## Background

Rapid weight gain (RWG) during infancy is one of the strongest risk factors for obesity later in childhood [1]. A growing body of evidence shows the incidence of infant obesity, especially in low-income infants, is rapidly increasing [2-6]. The first year of life is a critical period for reducing risk of obesity [7-12], particularly the first six months [13,14]. Rapid weight gain in the first six months of life is associated with a sharply increased risk of obesity later in life [15-18] and subsequent health consequences [19]. Unhealthy infant feeding practices may lead to rapid or excessive weight gain in early infancy [12,14,20] and a combination of formula feeding and early introduction of solids contribute to rapid/excessive weight gain [21-25]. Factors associated with rapid/excessive weight gain include socioeconomic status, maternal age, and infant feeding practices [20,26], which include formula feeding, age of introduction to solids, maternal responsiveness, and overfeeding [1,27-32]. Unhealthy mother-infant feeding practices contribute to rapid/excessive infant weight gain [33,34]. Adolescent mothers’ feeding behaviors are most directly related to infant weight gain in the first year of life [31,35,36]. Compared to adult mothers, adolescent mothers are less knowledgeable [37], less responsive, more controlling, and less skilled in infant feeding [38], which interferes with infants’ self-regulation, natural weight trajectory, and healthy growth during the first year of life [39], putting these infants at higher risk for developing obesity [40]. Low-income, adolescent, first-time mothers are also less likely to engage in infant-centered feeding (shared regulation of feeding within the mother-infant dyad) characterized by maternal responsiveness [41] (MR) (positive maternal recognition and responses to infant cues), positive feeding styles [42] (FS) (maternal guided approach to infant feeding), and healthy feeding practices (FP) [43] as recommended by the American Academy of Pediatrics (AAP) [44]. Infant-centered feeding is needed to reduce rapid/excessive gain in the first six months of life [45]. Infant-centered feeding fosters infant feeding self-regulation [46-49], which is associated with healthy growth (weight and length) and is crucial in reducing childhood obesity risk [50-52] and adverse health conditions later in life [53-56].

Few published intervention studies on the prevention or reduction of obesity in infants exist [57]. Practical early intervention strategies are needed to promote infant-centered feeding among adolescent mothers to prevent rapid/excessive infant weight gain in the first six months of life. The few studies published about the efficacy of interventions for obesity prevention in early infancy report mixed results [30,33,58-61]. One home-based study with primarily breastfed babies supported healthy infant growth through delay of introduction to solid foods [58], while a pilot education program with high income and educated participants (which consisted of five pediatrician messages and four coaching sessions by health educators) indicated a delay of solid foods with a trend in lower change in weight-for-length z-scores [57,59]. A double-blind, randomized educational intervention with one session on recognizing satiety cues and limiting volume of formula found no differences on weight gain, formula intake, or parental behavior [30]. Several other studies are in progress [33,61-67], but do not focus on adolescent mothers. This study proposes a highly accessible solution that addresses the unmet knowledge needs of adolescent mothers via an intervention (Tools for Teen Moms) (T4TM) to improve infant-centered feeding (MR, FS, FP) and infant growth. The proposed intervention addresses a deficit in the literature on infant-centered feeding to reduce rapid/excessive infant weight gain that exists for this high-risk population. The purpose of the study is to test a new social media intervention (T4TM) designed by the investigators. The intervention includes an educational web-application, accessible both via computers and smartphones, designed to increase infant-centered feeding through daily behavioral challenge activities, as well as additional resources related to infancy and motherhood, a discussion forum, and a messaging system for asking questions of a registered nurse. Participants receive daily cell phone text message reminders to log on to the website and complete that day’s challenge.

The ubiquity of technology in adolescents’ lives requires new pedagogical methods for interventions to reduce the risk of infant obesity that are adapted to the learning and information-seeking styles preferred by this population [68,69]. There is a dearth of outcome research on nutrition eHealth interventions targeting adolescents [68]. The ability to use technology to deliver interventions is evident: 77% of 12 to 17-year-olds own a cell phone [70-72]. During a six month study, adolescent mothers with infants under six months of age reported seeking health information and social support from online communities, posting 16,670 times, and spending an average of 102.25 hours on these websites [73]. The Pew Survey [71] reports teens regularly go on-line (94%), indicating this age group embraces technology and social media in their everyday lives [74,75]. Social media transcends space and time constraints [76], making health messages more accessible and enabling users to decide when, where, and how they want to receive information. Social media interventions have the ability to facilitate social connections and foster emotional support between adolescent mothers who may feel isolated or disconnected; however, there is a paucity of rigorously designed randomized controlled trials (RCT) of technology-based interventions in health care [77].

T4TM is the first targeted intervention delivered via a social media web-application that actively engages and coaches low-income adolescent mothers in infant-centered feeding to reduce rapid/excessive infant weight gain in the first six months of life. Our study is innovative in multiple ways: 1) it fills a significant gap in obesity research on infant-centered feeding related to MR, FS, and FP together and their contribution in infant accelerated growth and obesity [78]; 2) it promotes daily maternal behavior modification across six weeks for early obesity prevention [59,79]; and 3) it targets an understudied, vulnerable population (low-income, adolescent mothers) [80]. Tools for Teen Moms goes beyond Text4Baby [81], a website that provides infant feeding information to mothers via text messaging. Tools for Teen Moms includes daily behavioral challenges, text message reminders, discussion forums, and a repository of information and references as a comprehensive social media strategy. The design of T4TM differs in its use of: 1) persuasive technology guidelines for health behavior change; 2) challenges to intrinsically motivate participants [82] and support self-efficacy [83]; 3) public commitment and normative influence via social media streams [84]; and 4) inexpensive, easily integrated infant-centered feeding activities [82,83]. The novelty of T4TM is not only its design but also in its ability to affect one of the few potentially modifiable infant obesity risk factors [85-87]. Tools for Teen Moms expands on existing programs focused solely on nutrition via three key techniques: 1) interpreting and responding to infant cues while transitioning to solid foods; 2) providing an attentive and infant-centered authoritative feeding style; and 3) building skills to develop, implement, and sustain an infant-centered feeding plan.

### Aims and hypotheses

The aim of this study is to compare the effect of a social media intervention for low-income adolescent, first-time mothers of infants 2 months of age or younger, versus standard care on infant weight, maternal responsiveness, and feeding style and practices. Adolescent mothers with infants 2 months of age or younger will be assigned randomly to a control/usual care or intervention condition.

The usual Maternal Infant Health Program (MIHP) care only condition consists of voluntary home visits (one week postpartum, six weeks, and six months) and on-going as needed visits (up to nine during the infant’s first year of life) provided by a Registered Nurse (RN), Licensed Social Worker (LSW), Registered Dietician (RD), infant mental health specialist and/or paraprofessional. Maternal Infant Health Program interventions are based on participants’ individualized plans of care following in-home screening assessments. Content includes a flexible plan of care with visits based on identified domains for both the mother (e.g., family planning, transportation, housing, and breastfeeding support), and the infant (e.g., monitoring infant growth). For the T4TM plus usual MIHP care condition, participants get the same usual care treatment as the control group and also receive text messages for six weeks, reminding them to view the T4TM web-application and complete the behavioral challenges. Daily challenges cycle through a pre-determined schedule and focus on: 1) maternal-infant feeding interaction (maternal responsiveness, infant temperament, feeding style); and 2) feeding practices (e.g., delay of early introduction to solids; how much to feed babies) including the feeding environment (e.g., communication with baby, sitting down to eat, turning off the television). Participants also have the option to retroactively complete challenges posted in the last week. We hypothesize:

H1: The T4TM plus MIHP (intervention group) as compared to the MIHP only (control group) will exhibit a greater proportion of infants: a) with a growth in weight that falls below the 85th percentile of the WHO (World Health Organization) growth norms at three and six months, and b) that have a z-score change <0.67 in weight-for-age WHO norms over time periods one to three months, and three to six months [27,88].

H2: The T4TM plus MIHP (intervention group) as compared to the MIHP only (control group) will have: a) higher average maternal responsiveness scores, b) greater probability of using a positive feeding style, and c) greater average delay in introducing solid foods in keeping with AAP guidelines.

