## Methods/Design

### Overall study design

This randomized, experimental, short-term, longitudinal controlled trial uses a convenience sample of low-income adolescent first-time mothers of infants from four counties in Michigan. Participants are randomly assigned to the T4TM intervention or a control group with a retention goal of N = 40 participants per group by Time 3 data collection. Data are collected when infants are 4–8 weeks of age (Time 1), 10–12 weeks of age (Time 2), and 6 months of age (Time 3).

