### T4TM intervention

T4TM provides a new daily challenge over six weeks, a time frame selected to provide participants with enough opportunities to form the habit of visiting the T4TM web-application daily [122,123]. Participants log onto T4TM through their cell phones (or a computer), a technological requirement for the study that does not pose an undue burden on participants, especially as low-income households use social networks more frequently than adolescents in higher-income households [71,72]. Participants are encouraged to engage with T4TM as frequently as they like. Frequency of use and number of challenge completion will be logged by the application. Throughout the six-week intervention, participants will receive a daily text message, containing the challenge name and the URL to open the web-application directly through their smartphones. When the participants visit the T4TM page they will see: 1) the name of the challenge, 2) why the challenge is important, 3) tips to complete the challenge, 4) how many people have completed the daily challenge, and 5) a space to leave comments. In addition to the rotating challenges, adolescent mothers can browse T4TM for information about infant feeding, links to related topics, a discussion forum, and a place where they can receive expert advice from a RD or RN. When participants complete a daily challenge, they may click on the “I Did This” button to publicly acknowledge their accomplishment, which serves as a motivational feedback function as they observe other mothers’ completion of the challenges, thereby establishing healthy feeding practices as normative for the young mothers [124]. Participants continue to receive usual MIHP care during the intervention.

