### Procedures

Data are obtained by trained data collectors using both self-report questionnaires and anthropometric assessment. To ensure consistency and accuracy of data collection, a half-day intensive training session was held for data collectors prior to the collection of data, to be followed by a booster session in year 2. Training consisted of a standardized training guide and protocol including review of the instruments and measurement of infant recumbent length and weight. Telephone contact and email communication occurs between the project manager and the data collector and/or supervisor to facilitate open communication and fidelity to the protocol.

Intervals for data collection reflect time points (at infant age of 4–8 weeks, 3 months, and 6 months old) that align with both infant feeding recommended milestones and the intervention duration. For example, the third data collection occurs when the infant is 6 months old, when solids foods introduction is recommended.

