#### Infant outcome

**Infant growth** is the measurement of an infant’s weight and length plotted over time using *z* scores computed from the measures taken at T1 (baseline),T2, post intervention; and T3. Infant weights and lengths will be standardized as weight-for-age percentiles (WAP) and weight-for-age *z*-scores (WAZ), using WHO Anthro [140]. Relative weight gain (or loss) can then be calculated as the difference between WAZ scores at T3 and T1 [140]. Rate of growth proportional to birth weight and body composition (a weight-for-length index) will also be calculated. We expect a greater proportion of infants in the intervention group: 1a) will fall below the 85th percentile of the WHO growth norms at three and six months; and 1b) z score change <0.67 in weight-for-age WHO norms over time periods one-to-three months, and three-to-six months.

The infant’s weight and length is measured at all three time points to provide an objective measure of weight status. The infant is weighed in a clean diaper on an electronic scale and weighed to the nearest half ounce. Infant length is measured in the recumbent position. Digital scales are calibrated prior to weights being taken. These data will be entered into EpiInfo V3.4.3 to calculate weight-for-length z scores.

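### H1b applies one fixed 0.67 z-score cut to a first growth period that the visit windows do not deliver (2 to 8 weeks, against about 8.7), so the rapid-gain rate can vary with age at T1

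*Protocol article*

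**What the plan says.** In Aims and hypotheses, H1b defines a favourable infant result as a "z-score change <0.67 in weight-for-age WHO norms over time periods one to three months, and three to six months". The Infant outcome section repeats it almost word for word: "z score change <0.67 in weight-for-age WHO norms over time periods one-to-three months, and three-to-six months". The same cut serves both periods, and neither section scales the change to the time elapsed.

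The visit ages are given in several places:

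- Overall study design: data are collected when "infants are 4–8 weeks of age (Time 1), 10–12 weeks of age (Time 2), and 6 months of age".
- Procedures: visits are "at infant age of 4–8 weeks, 3 months, and 6 months old", which moves T2 from 10–12 weeks to about 13 weeks. The abstract also puts this visit at 3 months.
- T4TM intervention: "T4TM provides a new daily challenge over six weeks". The Data analysis section places T2 directly after the intervention ends.

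The Data analysis section compares infant age between arms at baseline and makes it a covariate only if a difference is seen. The Infant outcome section also describes a T3 minus T1 change in WAZ, but H1b does not use it.

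**The concern.** A yes/no outcome on change over a period needs that period to be the one observed, and to be roughly the same for every infant. Neither holds for the first H1b period. An infant weighed at 8 and 10 weeks has two weeks in which to cross the cut; one weighed at 4 and 12 weeks has eight. Weight-for-age standardisation removes average growth, but not the tendency of individual changes to spread out over time. That spread decides how many infants cross 0.67.

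Two things are at stake. First, the T1–T2 proportion would partly reflect when visits happened, and could not properly be reported as growth from one to three months. Second, the Sample size section lists estimating an effect size for a larger study among the trial's main purposes. A proportion with few events that depends on this trial's visit timing transfers poorly.

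**Working it through.** The plan gives no rate of rapid gain, no SD of WAZ change and no T1–T2 interval in weeks, so there is no figure of its own to reproduce. The check has an arithmetic part, which rests on the document, and a size part, which rests on stated assumptions.

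**Interval lengths (from the document).** One month = 365.25/12/7 = 4.35 weeks, so one to three months is 2 × 4.35 = 8.7 weeks, three months is 13.0 weeks and six months is 26.1 weeks.

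- Overall study design, with T1 "4–8 weeks of age (Time 1") and T2 "10–12 weeks of age (Time 2"): shortest 10 − 8 = 2 weeks, longest 12 − 4 = 8 weeks.
- Procedures, T2 at 3 months: 13.0 − 8 = 5.0 to 13.0 − 4 = 9.0 weeks.
- Six-week intervention, then T2: T2 falls at 4 + 6 = 10 to 8 + 6 = 14 weeks. To stay by week 12, T1 must be at 4–6 weeks, and the interval is 6 to 8 weeks.
- T2–T3, with T3 at "6 months of age (Time 3"): 26.1 − 12 = 14.1 to 26.1 − 10 = 16.1 weeks, or 13.0 if T2 is at 3 months.

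If visits fall uniformly and independently in the Overall study design windows (assumption), the T1–T2 interval averages 5.0 weeks, 75% of infants have less than 6 weeks, and 80% of the interval's variance comes from T1 timing.

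**Chance of exceeding the cut (assumed model).** WAZ change has mean 0 and SD 0.5 over 8.7 weeks, growing with the square root of time:

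P(t) = 1 − Φ(0.67 / (0.5 × √(t/8.7)))

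| Weeks | SD | 0.67/SD | P |
|---|---|---|---|
| 2 | 0.240 | 2.79 | 0.3% |
| 5 | 0.379 | 1.77 | 3.9% |
| 8 | 0.479 | 1.40 | 8.1% |
| 8.7 | 0.500 | 1.34 | 9.0% |
| 15 | 0.657 | 1.02 | 15% |

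Averaged over the uniform windows, P is 3.9%, against 9.0% at the nominal period: 0.039 × 40 = 1.6 infants per arm of 40, against 0.090 × 40 = 3.6. For an SD of 0.4 the rate falls from 4.7% to 1.5%; for 0.6, from 13.2% to 6.9%. If only intervals of 6 to 8 weeks occur, P runs from 5.3% to 8.1%, averaging about 6.3%, or 0.063 × 40 = 2.5 infants per arm.

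**Second model.** WAZ has SD 1 and a correlation that decays with time, r_t = r₈^(t/8), so P(t) = 1 − Φ(0.67/√(2(1 − r_t))).

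| r₈ (assumed) | 2 weeks | 8 weeks | T1 at weeks 4–5 | T1 at weeks 7–8 |
|---|---|---|---|---|
| 0.70 | 5.2% | 19.4% | 17.2% | 10.5% |
| 0.80 | 2.1% | 14.5% | 12.2% | 6.0% |
| 0.90 | 0.2% | 6.7% | 4.9% | 1.3% |

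The group rate is 1.6 to 3.7 times as high for infants seen early at T1 as for those seen late. Under the compound symmetry at 0.20 used for the sample size, the SD of change is √(2 × 0.8) = 1.26 and P is 29.8% at every interval.

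**Share of the individual result.** Under either time-dependent model, interval length explains under 1% of the variance of the yes/no outcome (about 0.9% with SD 0.5).

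**Would prorating the cut help?** Under the first model, a cut of 0.67 × t/8.7 gives P = 1 − Φ(1.34 × √(t/8.7)): 26% at 2 weeks, 15% at 5, 10% at 8 and 9% at 8.7. The dependence on timing reverses and the spread of rates widens.

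**The case against.** Three stronger readings are tempting, and the document supports none of them.

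- **That an infant's classification depends largely on T1 timing, or that late-enrolled infants are automatic successes.** Interval length explains under 1% of the individual outcome. With uniform visits only about 6% of infants have an interval under 3 weeks, and at the average of 5 weeks the assumed rate is 3.9%, not zero. The effect is on group rates.
- **That the comparison is biased.** Randomisation is balanced by county and should balance T1 timing in expectation. Nothing in the article ties visit timing to arm.
- **That the stated period can never be observed.** In four-week months, the pair at weeks 4 and 12 is exactly one and three months. With T2 at 3 months, the range of about 5 to 9 weeks includes 8.7.

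A further objection has force. The shortest intervals arise only if T2 comes before six weeks of intervention are complete, which conflicts with T2 following directly after it. On the 6-to-8-week reading, the loss is from 9.0% to about 6.3%, roughly one infant per arm. That tempers the size, but it also shows that the sections disagree on the interval the endpoint needs.

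Compound symmetry at 0.20 would remove the dependence altogether. It is a sample-size simplification, under which weights two weeks apart are no more alike than weights months apart, so it is a poor model of growth. Adjusting for exact days is often left to an analysis plan. Here, though, the article fixes the period, the cut and the windows, and they do not fit together. Its covariate rule tests for imbalance between arms, not unequal elapsed time within them.

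**Conclusion.** The point holds as a mismatch between the H1b period and the visit schedule. The visit windows permit 2 to 8 weeks, the Procedures section implies about 5 to 9, and the intervention timing implies 6 to 8 within the T2 window. One unscaled cut is applied throughout.

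The rapid-gain rate can therefore vary materially with age at T1. With an assumed SD of 0.5 over 8.7 weeks, the average rate falls from 9.0% to 3.9% under uniform visits, or to about 6.3% on the 6-to-8-week reading. The interval arithmetic is certain. The rates are illustrative, because the article gives no SD or interval-specific correlation of WAZ change.

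The harm is a lower event rate, added noise and a mislabelled period. It deserves correction, but does not threaten the validity of the randomised comparison.

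**What to change.** 1. Reconcile the visit ages and T2 timing across Aims and hypotheses, Overall study design, T4TM intervention, Procedures and Data analysis, so that one T1–T2 interval is defined.
2. In Aims and hypotheses and in Infant outcome, state H1b by the intervals observed, T1–T2 and T2–T3.
3. Make the early-growth analysis WAZ at T2, adjusted for WAZ at T1 and the exact days between the two weighings. Apply this adjustment in all analyses, not only when the arms differ at baseline.
4. If the 0.67 yes/no outcome is kept, report it as secondary with elapsed days as a covariate. Do not prorate the cut linearly by days.

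The cost is wording and one pre-specified model. It uses weights the trial already takes and their visit dates, with no new visits. The downside is that a continuous result is less directly comparable with publications that use the unscaled 0.67 cut; the secondary yes/no report keeps part of that link.

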### Participants and recruitment

To be eligible, a potential participant must: be low-income (≤185% federal poverty level in the United States and eligible for MIHP services), be between 15 and 19 years of age at time of enrollment, be a first time mom, have an infant two months of age or less, be a primary caregiver who feeds her infant at least once a day, have text messaging and web access, and have had a term birth (37 ≤ 42 weeks, 2500 ≤ 3750 grams birth weight). If either mother or infant has been diagnosed with an eating or nutritional condition, the dyad is ineligible. Staff members from MIHP offices in four Michigan counties target mother-infant dyads, providing information about the study to recruit mothers with infants or expectant mothers to enroll in the project.

Once eligibility is established, families are contacted for the initial data collection home visit where written informed consent is obtained. We have institutional approval to conduct this trial from the University Committee on Research Involving Human Subjects from Michigan State University.

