### Measures

#### Maternal outcomes

**Maternal responsiveness** is defined as sensitivity of the behaviors of a mother to her infant’s cues through expert judgment of what her infant needs [91-95]. These behaviors comprise a relationship skill set promoting mothers’ accurate recognition and response to infants’ feeding cues [96,97]. The Maternal Infant Responsiveness Instrument [125] is used to measure maternal responsiveness to infant cues; the scale is valid [126] and reliable (alpha = .83 and .87) [41,127]. We expect the intervention group to have higher scores than the control group.

**Feeding style** expresses the mother’s beliefs about and approach to guiding her infant’s feeding behaviors [97,98]. It also describes how (style) mothers feed their infants (authoritative, authoritarian, permissive, uninvolved) [99-101]. An adapted version of the Infant Feeding Styles Questionnaire (IFSQ) [128,129] is used to measure feeding beliefs and feeding style behaviors [42,43,97-99,129,130]. The IFSQ was pretested and validated with 150 African American first-time mothers with children ≤ 2 years of age [43]. Reliabilities for subscales range from .75 to.95 [128]. We expect the intervention group to score higher in the authoritative range than the control group.

**Feeding practices** are maternal behaviors relating to what is fed, where, how, and how often; they are essential for ensuring healthy eating habits throughout childhood [98,102-104]. The Infant Feeding Index (IFI) [131-134] identifies age-appropriate beverages and foods offered to the infant [135-138] and the appropriateness of feeding environment (i.e., support infant’s self-regulation) per AAP recommendations is a valid measure [131,133,135,136,139]. Of primary concern is the time at which solid foods are first introduced into the infant’s diet. We expect a longer average delay of introduction to solid foods that is closer to the AAP recommendation in the intervention group compared to the control group.

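### H2c averages age at first solids over every randomised infant, including any who had solids before assignment; this can only cost sensitivity, and a baseline restriction would avoid it (optional, low severity)

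*Protocol article*

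**What the plan says.** H2c (Aims and hypotheses) predicts a "greater average delay in introducing solid foods in keeping with AAP guidelines". The Measures section, under Maternal outcomes, makes the timing of first solids the main feeding-practice variable: "Of primary concern is the time at which solid foods are first introduced into the infant’s diet". It repeats the prediction as a comparison of averages: "We expect a longer average delay of introduction to solid foods that is closer to the AAP recommendation in the intervention group". Neither place limits the comparison to infants who have not yet started solids.

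Participants and recruitment requires the mother to "have an infant two months of age or less" and to "be a primary caregiver who feeds her infant at least once a day". The one stated exclusion is diagnostic: "If either mother or infant has been diagnosed with an eating or nutritional condition, the dyad is ineligible". Solids already given is not mentioned.

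Overall study design puts the first data collection at 4–8 weeks of infant age. Under Randomization, packets are randomised in advance, and data collectors learn the arm when they arrive at the home for the baseline visit. Data analysis applies intention to treat with imputed data to all analyses, evaluates feeding practices at all three time points including baseline, and uses baseline variables as covariates only where the groups are seen to differ.

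**The concern.** Up to two months of the infant's life pass before the intervention can act. An infant first given solids in week 3 and enrolled in week 6 contributes an age of 3 weeks to its arm's mean, whichever arm that is. Such values cannot respond to treatment. They also lie in the far low tail, so they dilute the mean difference and widen the SD together.

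Two features of the plan give this some weight. Delaying early solids is among the topics of the daily challenges, and the sample-size section names estimation of the effect size for a larger study first among the study's aims. A diluted H2c estimate would understate what the intervention does in infants whose introduction of solids can still be influenced.

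**Working it through.** **The plan's own figure.** The sample-size section gives 80 participants (40 per group), power 0.80, one-tailed 0.05, three measures and correlation 0.20. It states no effect size, so the number can only be solved backwards. The variance factor is [1 + (3 − 1) × 0.20]/3 = 0.4667, and d = √[2 × (1.645 + 0.842)² × 0.4667/40] = 0.38. That calculation is for infant growth. It makes no power claim for H2c, which has one age per infant.

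**Assumptions (none of these figures is in the article).**
- 40 infants per arm, one-sided 0.05, and an effect in infants still at risk that gives 80% power for a single measure: d = 0.561 by the two-sample t-test.
- Later introductions: mean μ of 12 to 20 weeks, SD s of 4 to 5 weeks.
- Introductions before baseline: mean 4 weeks, SD 1.5 weeks.
- Share p already on solids at baseline: 2%, 5% or 10%.

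**Formulas.**
- The mean difference is multiplied by (1 − p).
- Mixture SD = √[(1 − p)s² + p × 1.5² + p(1 − p)(μ − 4)²].
- The standardised effect is multiplied by (1 − p)s / mixture SD.
- The restricted analysis keeps d = 0.561 with 40(1 − p) infants per arm.

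**Worked case at 5%, least favourable (μ = 20, s = 4).** The variance is 0.95 × 16 + 0.05 × 2.25 + 0.0475 × 256 = 27.47, so the SD is 5.24. The multiplier is 0.95 × 4/5.24 = 0.725, d falls to 0.407 and power to 0.56.

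**Worked case at 5%, most favourable with a widened SD (μ = 12, s = 5).** The variance is 0.95 × 25 + 0.05 × 2.25 + 0.0475 × 64 = 26.90, so the SD is 5.19. The multiplier is 0.95 × 5/5.19 = 0.916, d falls to 0.514 and power to 0.74.

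| Share on solids at baseline | Power, all infants, widened SD (μ 12–20, s 4–5) | Power, all infants, dilution of the mean only | Power, restricted to infants without solids |
|---|---|---|---|
| 2% | 0.690–0.775 | 0.786 | 0.793 |
| 5% | 0.563–0.736 | 0.763 | 0.782 |
| 10% | 0.426–0.674 | 0.723 | 0.762 |

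The restricted analysis is at least as powerful in every row. Most of the loss comes from the widened SD, and the lowest figures need μ = 20 with s = 4, a gap of (20 − 4)/4 = 4 SDs.

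**Does the covariate rule deal with it?** Suppose 3 of 40 infants in one arm and 0 of 40 in the other already had solids. The uncorrected chi-square is 80 × (3 × 40)²/(40 × 40 × 3 × 77) = 3.12, p = 0.08, so a 5% screen would not trigger adjustment. With gaps of 12 to 16 weeks (μ = 16 to 20), the imbalance moves one arm's mean by 3/40 × 12 = 0.9 to 3/40 × 16 = 1.2 weeks. The effect assumed detectable is 0.561 × 4 = 2.2 to 0.561 × 5 = 2.8 weeks. Even when triggered, the rule adjusts for imbalance and does not change who counts as at risk.

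**The case against.** The strongest reply is that nothing in the article shows this happens often enough to matter. A reader might infer from the Background that adolescent mothers were chosen because they give solids very early. The text does not support that. It names early solids as a general risk factor with no age attached, describes adolescent mothers as less knowledgeable and less skilled in feeding, and justifies the population as understudied and vulnerable. Early relative to six months does not mean before eight weeks. This stands: the share may be close to zero.

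A reader might also infer that H2c is biased or its test invalid. It is not. Randomisation balances earlier introductions in expectation, the type I error is kept, and the intention-to-treat comparison answers a legitimate question about the enrolled population. Nor is a planned power being missed, because none is stated for H2c and it is not the primary infant outcome.

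Two further points stand in part. The article does compare feeding practices and type of feeding between arms at baseline, which gives some protection against imbalance but, as shown, can miss a small one. The analysis set for H2c might be refined in a fuller document; what this article states, however, is intention to treat for all analyses.

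Finally, restriction is not automatically safe. Feeding data are self-reported, and the arm can become known at the same visit. If solids status were recorded after disclosure, classification could differ by arm, a problem the full comparison does not have.

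**Conclusion.** The point holds as a matter of structure: entry at up to two months, no criterion on solids, a once-only outcome and an all-infants mean together let events before assignment count as H2c outcomes. The consequence is attenuation and extra variance, with no systematic advantage to either arm. The size is unknown. Under the stated assumptions, at 40 per arm, power falls from 0.80 to about 0.69–0.79, 0.56–0.76 and 0.43–0.72 at shares of 2%, 5% and 10%; the upper end of each range is dilution of the mean alone. The loss disappears if the share is zero. This is a low-severity, optional improvement to a non-primary outcome.

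**What to change.** State in Data analysis that H2c is tested in infants with no solids reported at baseline, by the same rule in both arms, counting only introductions after that visit. Record solids status at the baseline visit before the assigned group is disclosed; without that ordering, the restricted set is open to differential classification. Report infants already on solids at baseline separately by arm, and give the full intention-to-treat comparison as a sensitivity analysis. All other outcomes stay on the full intention-to-treat set.

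The cost is a sentence or two in the analysis section and attention to the order of steps at the visit, since feeding practices are already assessed at baseline. The H2c analysis loses a few infants: at 5%, 40 × 0.05 = 2 per arm. Its conclusion then applies only to infants who had not yet started solids. If no infant had solids at baseline, the two analyses coincide.
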